### Study hypothesis

Considering the facts that in our study area: (1) IPT of malaria provides substantial protection against anaemia and malaria in school children; (2) the level of SP resistance has no significant impact on the prophylactic efficacy [25]; and (3) SP-PQ is safe and as efficacious as SP, we hypothesize that antimalarial IPT with SP and SP-PQ will improve haemoglobin concentration, reduce anaemia prevalence, malaria incidence and parasitaemia, and improve nutritional status and school performance in school-aged children of DRCongo.

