### Design and sample size calculation

The study is an unblinded, randomised controlled trial, enrolling asymptomatic school children, either gender. At baseline, month four, and month eight, IPT with SP or SP-PQ is given. SP is administered as a single treatment dose. However, PQ is given as two doses with a 24-hour interval. IPT is administered at four month intervals in line with the long half-lives of the drugs and for compliance. Each treatment arm will be compared to the control group of untreated participants. Due to the prevalence of STH and schistosomiasis in the study area all participants are treated with albendazole or praziquantel according to the WHO guidelines [26]. Before the study, parents or guardians and children were informed about the objectives and the design of the study during organised meetings at schools.

Within each school, each schoolchild is randomly assigned to one of the two intervention groups or the control group as follows: IPT-SP, IPT-SP-PQ and no-treatment. Each study arm consists of one-third of all individuals.

To estimate the statistical power of our studies, we used an effect size of 0.56 g/dl mean Hb level improvement by the antimalarial IPT compared to the control treatment. This effect size was based upon a previous study.

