A previous study estimated the mean Hb concentration of 13.01 g/dl respectively in schoolchildren with IPT and 12.45 g/dl without [27]. The sample size of the study is all schoolchildren of two schools selected within the nearest schools to the regional hospital centre. The overall number of schoolchildren in the two schools is estimated to be 1,300 (650 in each school). By excluding 200 children of the sixth primary school year (100 per school), and accounting for 20% cancelation and 30% to 40% absenteeism, a realistic sample size of 616 individuals is reached for the complete IPT treatment schedule. Using this effect size and sample size, power estimates were performed by Monte Carlo simulation. In each run, a dataset was simulated assuming the within-subject variance and between-subject variability was 16, and putting in effect size to 1. The power was then estimated by fitting a linear mixed model to the data (Hb level versus treatment, time and time:treatment interaction) and testing the significance of the interaction term. The power is then equal to the fraction of times the interaction term was significant, using a significance level of 5%. A sample size of 616 offers 100% power to detect superiority between the control and the intervention groups. For the non-inferiority of SP versus SP-PQ, this sample size has over 91% power to detect a difference in effect less than 0.27 g/dl (<50%).

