### Statistical analysis plan

The effect of the type of intervention (either IPT versus the controls, or SP versus SP-P) will all be analysed using linear mixed model analysis. In each analysis, Hb concentration is modeled versus time, testing whether the change of Hb concentration over time differs between the two types of intervention. In each case, a linear mixed model is fitted with Hb concentration as outcome variable, and fixed effects including the type of intervention (indicator variable), time and the interaction between them. In these models, the effect of interest is the interaction between intervention and time, which formally tests the null hypothesis that the change in Hb concentration with time is the same in all interventions. Significance of the interaction term is tested using the F-test with a Kenwardroger correction for the number of degrees of freedom. As the study includes several (longitudinal) measurements within the same individual, and since the individuals cluster within schools, the dependency between individuals will be accounted for by including random effect terms into the model. More particularly, the model will include random effects (intercept and slope) for individual, nested within the random effect of school. An additional advantage of this technique is that it gives unbiased results in case individuals are lost to follow-up during the study.

Analysis of the data will be performed using the nlme package from the statistical software R or the proc mixed procedure from the software package SAS. All statistical analyses will be performed in close collaboration with StatUa, the Center for Statistics at the University of Antwerp.

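### SP versus SP-PQ is powered as non-inferiority with a 0.27 g/dl limit, but the stated analysis is a test of equality that never uses the limit

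*Protocol article*

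**What the plan says.** Two sections of the protocol article deal with SP versus SP-PQ.

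- **Design and sample size calculation.** The trial is sized around "an effect size of 0.56 g/dl mean Hb level improvement by the antimalarial IPT compared to the control treatment". For the two active arms it says: "For the non-inferiority of SP versus SP-PQ, this sample size has over 91% power to detect a difference in effect less than 0.27 g/dl", and adds that this is under 50%. The same section defines power as the proportion of simulated datasets in which the treatment-by-time interaction is significant at 5%.
- **Statistical analysis plan.** One method covers both IPT versus control and SP versus SP-PQ: a linear mixed model for Hb with intervention, time and their interaction. The interaction is the effect of interest, "which formally tests the null hypothesis that the change in Hb concentration with time is the same in all interventions". It is assessed by an F-test with a Kenward-Roger correction. The section gives no limit, confidence-bound rule, one-sided hypothesis or separate alpha for SP versus SP-PQ.

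**The concern.** A non-inferiority claim needs the data to exclude a deficit as large as the limit. The null hypothesis is that the new or simpler option is worse by at least that amount, and rejecting it supports the claim. The F-test has a different null, no difference at all, and it has no direction. Rejecting it shows that the arms differ. Failing to reject it shows only that the data did not separate them.

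The plan therefore states a non-inferiority aim for SP versus SP-PQ but gives a test that cannot deliver it. Unless a rule is added, the only apparent route from this test to a non-inferiority statement is to treat non-significance as similarity. That route rewards imprecision: the noisier the Hb data, the more often a truly inferior arm would pass. Comparing SP with SP-PQ is a named secondary objective and one of only two comparisons for which the article quotes power.

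**Working it through.** **Inputs from the article**
- Limit 0.27 g/dl and effect 13.01 - 12.45 = 0.56 g/dl, so 0.27/0.56 = 48%. This agrees with the article's remark that the limit is under 50%.
- Sample size: (1,300 - 200) × 0.80 × 0.70 = 616, which reproduces the stated figure at 30% absenteeism. With 1:1:1 allocation this is 616/3 ≈ 205 per arm.
- Visits at months 0, 4, 8 and 12, and a 5% level.

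**Can the stated 91% be reproduced?** No. The sentence giving a variance of 16 does not make clear whether this is within-subject, between-subject or both. It also sets the effect size to 1. Neither the time scale of the effect nor the alpha for non-inferiority is given. I therefore take the 91% at face value and solve backwards.

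**Case A: 91% read as power to detect 0.27 g/dl, two-sided 5%**
- SE = 0.27 / (1.960 + 1.341) = 0.082 g/dl.
- Implied SD of change = 0.082 / √(2/205.3) = 0.83 g/dl.
- The equality test is non-significant for observed deficits up to 1.96 × 0.0818 = 0.160 g/dl. At that point the 95% bound is 0.160 + 0.160 = 0.321 g/dl, beyond the limit.
- A margin rule passes only observed deficits below 0.27 - 0.160 = 0.110 g/dl.
- So an observed deficit between 0.110 and 0.160 g/dl is non-significant but does not show non-inferiority.
- If the true deficit is 0.27 g/dl: P(non-significant) = Φ(1.96 - 0.27/0.0818) = Φ(-1.34) ≈ 9%. The margin rule falsely passes Φ(-1.96) = 2.5%.

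**Case B: assumed residual variances, random-intercept model**

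With time scaled to 0, 1/3, 2/3, 1, the sum of squares about the mean is 0.556. With complete data the random intercept cancels, so SE = √[(σ²/0.556) × 2/205.3].

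| Assumed residual variance, (g/dl)² | SE, g/dl | P(non-significant) at a true deficit of 0.27 g/dl |
|---|---|---|
| 0.5 | 0.094 | Φ(1.96 - 2.88) = 18% |
| 1.0 | 0.132 | Φ(1.96 - 2.04) = 47% |

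The article also plans a random slope. Any slope variance above zero would raise the SE and these percentages.

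**Power under the margin rule.** If the arms are truly equal, the margin rule succeeds with probability Φ(0.27/SE - 1.96). That is 91% in case A, 82% at variance 0.5 and 53% at variance 1.0.

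**The case against.** The strongest defence is that this is a condensed article. The same fitted model yields the SP minus SP-PQ contrast and its confidence interval, and a separate analysis plan could compare that interval with 0.27 g/dl. This would be decisive if the section were silent on the comparison. It is not: it names SP versus SP-PQ and fixes an equality null and an F-test for it. The mismatch with the sample size section is on the page.

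Other parts of the defence do stand, and they limit what can be said.

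- **Intended misuse.** A reader might infer that the trial team will declare non-inferiority from a non-significant test. The article does not say so; it says nothing about how such a result will be interpreted. Only *could* is justified.
- **A far larger error rate.** Reading the 16 as residual variance in (g/dl)² gives SE 0.53 and a non-significant test in 92% of trials at a true deficit of 0.27 g/dl, and 82% at 0.56 g/dl. Under that reading, power for 0.56 g/dl between two arms would be about 18%, whereas the article reports 100% for superiority. The reading does not fit the article's own figures, so I do not rely on it.
- **The 91% as a probability of non-significance.** It lies close to that 92%, but this is number-matching. It depends on the same variance reading and conflicts with the article's definition of power as the fraction of significant tests.
- **A contradiction on direction.** The study hypothesis section says "SP-PQ is safe and as efficacious as SP", which reverses the order in "For the non-inferiority of SP versus SP-PQ". The former is listed among the facts taken as given, so it is not a rival test hypothesis. The direction should be stated more clearly, but there is no firm contradiction.
- **Two ineffective arms passing as alike.** The article compares each active arm with untreated control, so this would show within the trial. A formal superiority condition or an analysis restricted to full courses is good practice that an article may leave to the full plan.

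**Conclusion.** The concern holds in a limited form. SP versus SP-PQ is planned as non-inferiority with a 0.27 g/dl limit, but the stated test is of equality and does not use the limit. The article does not call 0.27 g/dl a margin; placed beside non-inferiority, it has no other workable meaning.

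If non-significance were taken as non-inferiority, the false-claim rate at a true deficit of 0.27 g/dl would be about 9%, against 2.5% for a margin test. That figure assumes the stated 91% is correct and refers to a two-sided 5% test. It rises to 18% and 47% for residual variances of 0.5 and 1.0 (g/dl)², which are my assumptions, as are the random-intercept model, complete data and 205 per arm. The mismatch itself depends on none of these numbers.

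The comparisons of IPT with control are unaffected: an equality test suits a superiority question. What is at stake is a secondary objective, and the point must be settled before any non-inferiority claim is made.

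**What to change.** For SP versus SP-PQ, replace the F-test with a rule fixed before the data are examined and taken from the same mixed model: SP is non-inferior to SP-PQ if the lower limit of the two-sided 95% confidence interval for (SP minus SP-PQ) in Hb change at month 12 lies above -0.27 g/dl.

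- State the direction (SP tested against SP-PQ as reference) and the alpha (one-sided 2.5%, matching the two-sided 95% interval).
- Keep the equality F-test for the comparisons with control.
- Interpret the result alongside each arm's comparison with control.
- Restate the power for SP versus SP-PQ as the probability of meeting this rule, with the variance assumed.

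The change is one of wording and uses existing model output; no extra data are needed. The cost is that non-inferiority becomes harder to claim. If the arms are truly equal, the equality test is non-significant in 95% of trials at any noise level, whereas the margin rule succeeds in 91%, 82% or 53% under the three precision cases in the working.

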### Medicines accountability procedures

The study site maintains the study drugs under adequate security. Study drugs sent to the study centre are verified by the investigator or designee; the amount sent and the exact supplies received are documented by signing and dating the appropriate shipping documents. Study drugs are dispensed as per the randomization list to each patient who meets the enrolment criteria. The investigators or designees record the patient’s number, patient’s initials and date dispensed on the Drug Accountability Form. The investigators maintain an accurate running accountability of the study drugs. At the end of the study, final disposal of the unused drugs will be decided by the sponsor after final reconciliation has been made.

### Case report form

All data and observations are documented and entered in the CRF. For this study, the CRF allows identification of the study site and patient; recording of the selection and inclusion of patients in the study; recording of all data collected at each different study visit; recording of possible AE and any suspension of the study. Participants are identified by their initials and a study identification number on the CRF. When recording data on the CRF and entering the data in the database, confidentiality and security of the forms are ensured at all steps. All corrections are made on CRFs by striking through the incorrect entry with a single line and entering the correct information adjacent to it. The correction is initialed and dated by the investigator. Additional records are kept in the clinical and laboratory record books at the core facility in Kinshasa. The investigators verify data at each study visit.

### Randomisation and treatment allocation

Children fulfilling the inclusion/exclusion criteria will be assigned a sequential study number and will be treated according to a predetermined randomization list of blocks of varying size per school. Within each block each schoolchild will randomly be assigned to one of the two intervention groups or the control group in 1:1:1 balance. Sealed envelopes labeled with the school unique code and containing the list with the treatment allocated to the participants will be provided according to the above mentioned list and opened at the moment the children are recruited.

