#### *Exclusion criteria*

Participants with at least one of the following criteria are excluded:

1. Children of the sixth primary school year.

2. Participation in any other investigational drug study (antimalarial or others) during the previous 30 days.

3. Known or suspected hypersensitivity or serious adverse events (AE) to the study drugs.

4. Malaria symptoms at baseline irrespective of the severity [see Additional file 1].

5. Febrile conditions caused by diseases other than malaria at the first visit.

6. Decompensated anaemia.

7. Illness or conditions, such as hematologic, cardiac, renal, hepatic diseases, which in the judgement of the investigators would place the subject at undue risk or interfere with the results of the study, including known glucose-6-phosphate dehydrogenase deficiency and sickle cell.

8. Body weight <14 kg.

9. Children with major chronic infectious diseases (HIV, tuberculosis, and so on).

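### As worded, school-labelled envelopes that hold a list of allocations and are opened at recruitment do not protect allocation concealment in this unblinded trial

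*Protocol article*

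**What the plan says.** In the protocol article, Randomisation and treatment allocation fixes four things:

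- **Numbering.** "Children fulfilling the inclusion/exclusion criteria will be assigned a sequential study number".
- **Sequence.** They are then "treated according to a predetermined randomization list of blocks of varying size per school", with 1:1:1 balance within blocks. The block sizes are not given.
- **Envelopes.** "Sealed envelopes labeled with the school unique code and containing the list with the treatment allocated to the participants" are used.
- **Opening.** These are "opened at the moment the children are recruited".

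Design and sample size calculation adds the setting. "The study is an unblinded, randomised controlled trial", and the unit of randomisation is the individual: "Within each school, each schoolchild is randomly assigned to one of the two intervention groups or the control group". The control arm is untreated. Under Exclusion criteria, item 7 covers illnesses or conditions "which in the judgement of the investigators would place the subject at undue risk or interfere with the results of the study". Trial status is given as recruiting.

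**The concern.** Concealment means that whoever decides on a child's entry, and on the order of entry, does not know which arm comes next. Here the envelope is identified by school rather than by child, and its content is a list covering several participants. If it is opened when the first child is recruited, the same sheet shows what the following study numbers will receive.

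A visible arm is fully informative in an open trial with an untreated control. Because numbers are given in sequence, the recruiter could change who comes next, or how a discretionary exclusion is judged, knowing the arm. Varying block sizes hinder guessing from past allocations, but they do nothing when the sequence itself can be read. Every comparison in the trial rests on the randomisation, and selection at entry cannot be fully repaired by modelling.

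**Working it through.** The plan states no figure on concealment, so there is none of that kind to reproduce. The check is a reading of the text, plus a count of how many allocations would be visible under each reading.

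**1. Reading the text**

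| Feature | Text as written | What concealment would need |
|---|---|---|
| Label | School code | Identifier of one child, or a list kept closed until enrolment ends |
| Content | A list, participants in the plural | One allocation, or the same condition on opening |
| Opening | When children are recruited | After that child (or all children) are irrevocably entered |
| Numbering | Sequential, once criteria are met | Compatible with either |

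The article nowhere describes individual or numbered envelopes, central allocation, or a rule that a school's enrolment must be closed first.

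**2. Children per school**

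Inputs from Design and sample size calculation: 1,300 children, less 200 in the sixth year, 20% cancellation, 30% to 40% absenteeism.

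- (1,300 − 200) × 0.8 × 0.7 = 616. This reproduces the stated sample size, at 30% absenteeism.
- At 40% absenteeism: 1,100 × 0.8 × 0.6 = 528.
- Per school, assuming an equal split: 616 / 2 = 308.

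**3. One list per school**

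All allocations but the first are known before the child is recruited: 307 / 308 = 99.7%. The count of children hardly matters. With 528 / 2 = 264 per school it is 263 / 264 = 99.6%. With 880 / 2 = 440 (cancellation only) it is 439 / 440 = 99.8%.

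**4. One envelope per block**

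In this milder reading only the first child of each block is concealed, so the share known is 1 − (blocks / 308). Block sizes are assumed, since none are given. The number of blocks is the mean of 2,000 simulated lists of 308.

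| Assumed block sizes | Blocks per school | Share known in advance |
|---|---|---|
| 3, 6 | 68.8 | 78% |
| 3, 6, 9 | 51.6 | 83% |
| 6, 9, 12 | 34.7 | 89% |

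**5. One envelope per child**

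No later arm is disclosed. A recruiter who remembers past allocations and always guesses the arm used least so far would be right about 53% to 58% of the time under the same assumed block sizes, against 33% by chance. Some predictability remains, as in any unblinded trial with blocks, but nothing is read from a sheet.

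**The case against.** Five counter-arguments deserve a hearing.

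- **The wording allows a harmless procedure.** Both the envelopes and the children are in the plural. The text could describe a single opening after all eligible children of a school have been numbered, which would preserve concealment, or loosely describe one envelope per allocation. The first possibility stands as a possibility, but the article does not state it and describes numbering as children qualify. The second fits poorly with a school label and a list.
- **A journal article condenses.** Opacity, numbering of envelopes and opening logs are details that an article may leave to the full protocol, and their absence is not the point here. The point rests on what is stated: the label, the list and the time of opening.
- **The scope for steering is limited.** Eligibility comes before numbering, recruitment aims at nearly all children of two schools, and most exclusions are factual. This reduces selective inclusion. It does not prevent a change in the order of entry, and exclusion 7 remains a judgement.
- **A reader might infer that concealment was broken.** The document does not support that. It shows a procedure that permits foreknowledge, not how staff used it.
- **A reader might try to express the harm as a haemoglobin bias set against the 0.27 g/dl margin.** That is not supported either. The analysis tests the time-by-intervention interaction, so a shift in baseline mean is not a bias of equal size in the effect. Any bias in change would arise indirectly, for instance through regression to the mean. Moreover, 0.27 g/dl belongs to SP versus SP-PQ, whereas the planning effect for treated versus untreated children is 0.56 g/dl. The article gives no basis for how many children might be steered, or how they would differ.

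**Conclusion.** The concern holds as a defect in the written procedure. Unless every child in a school is already irrevocably enrolled and numbered when the envelope is opened, which the text does not say, the recruiter can see later children's arms and the varying block sizes give no protection.

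The extent can be stated only as visibility. It is nearly all of about 308 allocations in a school if one list covers it (equal split of 616 assumed), or roughly 78% to 89% if each envelope covers one block (block sizes assumed). No size of bias can be derived. The remedy is cheap and the trial was still recruiting, so this is worth correcting rather than merely noting.

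**What to change.** For remaining recruitment, adopt one of two procedures and write it into the protocol:

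1. One opaque, sealed envelope per child, labelled with school code and sequential study number, opened only after consent, eligibility and baseline haemoglobin are recorded.
2. A stated and enforced rule that each school's list is opened only after all of its children are irrevocably enrolled and numbered. If this is already the practice, one sentence saying so settles the point.

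For children already enrolled, compare baseline haemoglobin and parasitaemia by arm and by enrolment order, and report the result. A clean comparison is reassuring but does not prove that concealment held.

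The cost is a small amount of printing and an opening log. The randomisation list, with its 1:1:1 ratio and varying blocks per school, stays as it is. The one proviso is that unused entries which recruiting staff have already read are not concealed again by sealing them, and would need a fresh draw under the same scheme.
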